#### Assessment of headache days

Headache days will be calculated by the app based on the data entered by the patient.

#### Assessment of headache episodes

Headache episodes will be assessed based on the drug intake for the treatment of headache episodes documented by the patient in the app.

#### Assessment of severity of headaches

The severity of headache will be assessed based on a 4-point verbal rating Likert scale with no headache, mild headache, moderate headache, and severe headache.

#### MIDAS

Disability caused by headache will be measured by the MIDAS questionnaire [14, 15]. The patient will answer a paper-based version of the questionnaire. Answers will be copied by trained study personnel to the eCRF version of the questionnaire. The calculation of the MIDAS score will be performed automatically.

#### DASS

Psychiatric comorbidity will be assessed at the trial site with the help of the DASS questionnaire [16]. The patient will answer a paper-based version of the questionnaire. Answers will be copied by trained study personnel to the eCRF version of the questionnaire. The DASS score will be calculated automatically

#### External control group

Basic data capture will be performed at participating sites directly and entered using the CDMS. As patients agree to be contacted after 6 and 12 months by the ZKSE follow-up team directly, sites will transfer the personal data to the follow-up team. Personal data will be stored separately from other medical data entered in the CDMS or the app and only members of the follow-up team have access to this data to contact the patients.

### *Plans to promote participant retention and complete follow-up {18b}*

Patients will receive monthly unspecific messages for motivation. Patients have three planned study appointments after randomization within the following 12 months. The most important data (medication intake and days with migraine/headache) will be entered daily and will be saved on external servers almost in real time. The daily data entry time ranges from 2 to 5 min. Due to the fact that app compliance usually drops within 1 year, we have implemented a standardized way to contact patients, if their compliance declines below 80%. Furthermore, daily reminders will directly address the need for data entry to the patients.

Patients who terminate the study prematurely or who are withdrawn from the trial but gave consent to be contacted after the study end will have the opportunity to fill in a follow-up questionnaire at the end of the overall trial. If patients withdraw consent, all data collected up to the time of revocation will continue to be processed provided this serves to answer the scientific question.

### *Data management {19}*

The ZKSE will be responsible for data quality management and monitoring of this trial. As a full member of the national Network of Coordinating Centers for Clinical Trials (KKS Network; http://www.kks-netzwerk.de/), the ZKSE has adapted all harmonized Standard Operation Procedures (SOPs) to the local conditions. The ZKSE is an institution that is independent from the other trial staff.

To ensure accurate, complete, and reliable data, the ZKSE will:Perform user acceptance test for the app and the clinical data management system (CDMS)Create and validate a database for Electronic Data Capture (EDC) to review and evaluate the documentation of the app and CDMS data in time, and take other measures of central data monitoringConduct start-up training session during the initiation visit to instruct the investigators and the study team on the trial and the software programs usedProvide instructional material to the study sites, including training for the software programs

Despite the low-risk nature of the intervention (feedback messages in the headache app), the study will have a data safety monitoring board (DSMB).

Data entry in the app will be checked for implausibility in real time providing direct feedback to the patient and increasing data quality. Wherever data is captured and stored, technical and organizational measures are implemented to protect data adequately against misuse and loss. App data will be exported monthly. The CDMS used by the ZKSE has an integrated audit trail and is a GCP-compliant data management system. Data entry field from the eCRF have integrated range checks wherever this is appropriate. In addition, entered data will be checked for implausibility and queries will be addressed in a standardized manner to participating sites.

To ensure data quality and comparability during the course of the trial, software version updates are strictly controlled and limited to the minimum. In summary, only updates that are essential for a trouble-free operation of the app are allowed. Updates, which are usually common in commercial applications such as user interface visualization, implementation of additional features, or questionnaire adaptions, are not part of the study version of the app.

### *Confidentiality {27}*

Data protection will be ensured at all stages of data collection, transfer, processing, and analysis in accordance with laws and regulations of the Federal Republic of Germany and with international standards. The patients will be informed about the study, including the collection, handling, and storage of data, before they sign a written informed consent for study participation. They will be informed about their rights, especially regarding withdrawal of their consent. Disclosure of personal data, especially to third countries outside the European Union (EU) or the European Economic Area (EEA) — without an EU conformity decision — is only permissible with the consent of the study patients. Integrity, confidentiality, and availability of personal data will be ensured in accordance with the General Data Protection regulation (GDPR). Both ZKSE and Curelator will take technical and organizational measures, in keeping with the requirements of the relevant data protection regulations, to protect data adequately against misuse and loss. The principle of purpose limitation of data collection, transfer, and evaluation will be respected and data confidentiality will be guaranteed for employees as well as for sub-contractors/data processor. Medical Study data will be stored on servers located in the EU. Relevant processing of personal data outside of the EU/EEA necessary for the conduction of the study or for provision of the app to study participants will be safeguarded, either by EU conformity decisions or standard contractual clauses. Data sovereignty at the end of the study, including data collected by the app, will be kept by the affiliation of the coordinating investigator.

Only those study staff members are granted access to study data who actually need access to fulfill their tasks within the scope of the study. Access is subject to technical and organizational measures that prevent unauthorized access. Within the scope and for the purpose of this study, all personal data will be stored in pseudonymized form. In order to be able to contact patients to reset the password in the event of a password loss, the name and email address are collected in the app and stored in a non-pseudonymized form. The email with the password reset link is generated automatically so that no employee accesses the name and email address and processes them manually.

After the end of the study, Curelator will delete or return all personal data in its possession except for the extent where Curelator is retaining support-related data, including customer support tickets and other support-related information. This data will contain the patients’ names and their email addresses, but will not be connected to any medical data, and will be kept for 10 years at the longest. After this retention period, all data will be deleted. At the ZKSE, study relevant data will be archived for 10 years after the end of the study according to GCP requirements, before it will be deleted or anonymized. The confidentiality of the study participants will be guaranteed by pseudonymization of patient data both in the EDC system (Clincase) and in the app.

### *Plans for collection, laboratory evaluation, and storage of biological specimens for genetic or molecular analysis in this trial/future use {33}*

Not applicable as no genetic or molecular analyses are part of this trial.

## 
Statistical methods

### *Statistical methods for primary and secondary outcomes {20a}*

The confirmatory analysis on the intention-to-treat (ITT) analysis set will be performed using a generalized linear mixed effects model with the prognostic factors of the randomization as covariates (site as random effect and age, sex, indication, and treatment arm as fixed effects).

Demographic and baseline characteristics will be presented for the interventional and control group by means and standard deviation (SD) for interval scaled data and by median and frequency given in percentage for ordinal data. Minimum and maximum as well as confidence intervals will be reported where appropriate.

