### Trial design {8}

This trial will be conducted according to the professional code for physicians in Germany §15 and is designed as a randomized, controlled, parallel, allocation-blinded multicenter, prospective trial with two arms. The effects of providing feedback to migraine patients regarding their self-reported use of migraine medications will be monitored using the app “N1-Headache” on the development of MO or MOH over 12 months after randomization.

Patients with qualifying migraine or a history of MO(H) will be recruited in different ways: First, through their physician at a participating headache center or medical practice. Second, through an advertisement for this trial sent by Curelator to German-speaking users of the public available Curelator app, directing interested patients to a participating site. Third, through cooperation with the German Headache Society (DMKG) and the MigräneLiga e.V, a self-help organization who will provide information about the trial within the respective section on their homepage. In addition, some study sites might publish a pre-approved template on their homepage to inform about the trial.

Informed consent will be obtained in the participating center through the investigator and a screening for the inclusion and exclusion criteria will be carried out. Medical history will be assessed for the determination of headache type and current treatment as well as actual medication intake. To facilitate the documentation of medication, the attack aborting medication documented during the screening visit will be handed out to patients as a printout to be entered in the app.

After patients have completed a screening phase of 28 days with a sufficient level of compliance (≥80% days of recording headache and medication use) and if the inclusion and exclusion criteria are still fulfilled, they will be allocated to one condition (migraine patients or post-MO(H) patients) and subsequently randomized into one of the two study groups (control group or intervention group). The control group will receive unspecific messages providing information on general trigger factors or latest migraine research highlights. The intervention group will receive the same unspecific messages and also direct feedback on their medication use through warning messages when predefined limits of frequent medication use are reached or passed.

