#### Screening

Before screening, written informed consent will be obtained prior to enrollment and all trial-related procedures. Date of informed consent, subject age, gender, and reason for ineligibility (if subject is not eligible) will be documented. After screening for assessable inclusion and exclusion criteria, the patient will be trained for all relevant aspects of function and data entry with the app. Current headache treatment and medical history will be documented. In the upcoming screening phase of 28 days, the patient will use the app for data entry only. No message will be generated within the screening phase. Within the screening phase, the compliance of the patient to use the app on a regular basis will be calculated by the app. The level of compliance is one inclusion criterion necessary for randomization at baseline visit and has to be ≥ 80%.

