### *Sequence generation {16a}*

In order to achieve comparable groups, patients in each category will be allocated by concealed central randomization. A 1:1 block randomization of variable block length with stratification by indication, site, age (≤ or > 30 years), and sex will be performed to achieve balanced factor distributions for these relevant predictors. The randomization will be conducted centrally by the Center for Clinical Trials Essen (Zentrum für klinische Studien Essen; ZKSE) using a Web-based randomization tool with an audit trail (ALEA) and each patient who is randomized will be part of the ITT analysis set.

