#### Outcome assessment

Relevant clinical data and additional lifestyle factors include information about depression, anxiety disorder, chronic back pain, sport activities, smoking, and drinking behavior as well as shift work.

The primary outcome is MO or MOH defined according to International Classification of Headache Disorders (ICHD-3, 8.2) criteria of MO and MOH [13]. According to ICHD-3, MO is defined as regular overuse of acute or symptomatic headache medication (on ≥ 10 days/month with specific migraine medication or ≥15 days/month of simple analgesics) for more than 3 months and MOH is defined as headache occurring on 15 or more days/month in a patient with a pre-existing primary headache and developing as a consequence of MO. In this study, the primary endpoint is reached when the intake thresholds or headache days are exceeded for ≥ 3 months [8].

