### *Methods for additional analyses (e.g., subgroup analyses) {20b}*

Predefined subgroup analyses will be performed in the strata sex, age, medication/medication intake, and number of headache days at baseline.

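### The confirmatory analysis does not adjust for baseline acute-medication days or headache days, although every randomised patient records them and the endpoint is a threshold on the same counts: a loss of efficiency, not of validity

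*Protocol article*

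**What the plan says.** All references are to the protocol article.

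- **Statistical methods {20a}, opening paragraph.** The confirmatory ITT analysis is a generalized linear mixed model "with the prognostic factors of the randomization as covariates". The terms are then listed: "site as random effect and age, sex, indication, and treatment arm as fixed effects". They match the randomisation factors in Sequence generation {16a}: "stratification by indication, site, age (≤ or > 30 years), and sex will be performed".
- **Statistical methods {20a}, Primary outcome.** The arms are compared separately in each category by Pearson's chi-square or Fisher's exact test, with no covariates. An additional conditional logistic regression for the odds ratio is to account for prognostic variables that are not named.
- **Screening.** "In the upcoming screening phase of 28 days, the patient will use the app for data entry only", and no messages are sent in that period. Trial design {8} makes a compliance of at least 80% of "days of recording headache and medication use" a condition for randomisation.
- **Outcome assessment.** "the primary endpoint is reached when the intake thresholds or headache days are exceeded" for at least three months. The intake threshold is at least "10 days/month with specific migraine medication or" at least 15 days of simple analgesics.
- **Additional analyses {20b}.** Predefined subgroups include "medication/medication intake, and number of headache days at baseline".

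**The concern.** The endpoint asks whether a patient's monthly count of intake days or headache days stays past a fixed limit. A patient who enters close to the limit has less far to go than one who enters well below it, so the baseline count is a natural prognostic variable. The trial measures it before randomisation, in everyone, with the same instrument as the outcome. The subgroup plan shows that the sponsor considers these variables relevant.

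The covariates that are listed probably explain less. Indication separates only migraine from post-MO(H) patients, so it is constant within each per-category test. Site, age and sex remain. At stake are some power in a trial planned at 80%, and the ability to correct a chance difference between arms in a likely important risk factor.

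**Working it through.** **Inputs from the protocol** (Sample size {14}, unless noted): two-sided alpha 0.05 (sidedness from {20a}); power 0.80; control and intervention rates 10% and 4% (migraine), 40% and 25% (post-MO(H)); 283 and 152 per arm; 1:1 allocation ({16a}).

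**Input not in the protocol:** the prognostic strength of the baseline count. It is assumed, and shown as a range.

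**1. Reproduce the stated sample size.** Pooled two-proportion z-test, per arm:

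n = [1.960·√(2·p̄(1−p̄)) + 0.842·√(p1(1−p1) + p2(1−p2))]² / (p1−p2)²

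- Migraine, p̄ = 0.07: (1.960·√0.1302 + 0.842·√0.1284)² / 0.0036 = 282.7, so 283.
- Post-MO(H), p̄ = 0.325: (1.960·√0.43875 + 0.842·√0.4275)² / 0.0225 = 151.9, so 152.

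Both match. The calculation is for an unadjusted comparison and takes no credit for covariates.

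**2. Expected events at those sizes.**

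- Migraine: 283 × 0.10 + 283 × 0.04 = 28.3 + 11.3 ≈ 40.
- Post-MO(H): 152 × 0.40 + 152 × 0.25 = 60.8 + 38.0 ≈ 99.

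**3. Completeness of the baseline count.** 80% of 28 days is 22.4, so at least 23 days are recorded and up to 5 may be missing. Every randomised patient has a usable count, but it needs scaling to the days recorded.

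**4. Power with and without the covariate.** 4,000 simulated trials per row; marginal event rates held at the planned values; one standardised normal baseline covariate; Pearson test against the likelihood-ratio test from a logistic regression adjusted for the covariate. AUC is in the control arm. Simulation error is √(0.8 × 0.2/4000) ≈ 0.6 points.

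| Category | Log OR per SD (assumed) | AUC | Power, unadjusted | Power, adjusted | Conditional OR |
|---|---|---|---|---|---|
| Migraine | 0 | 0.50 | 0.813 | 0.815 | 0.375 |
| Migraine | 0.5 | 0.64 | 0.815 | 0.828 | 0.369 |
| Migraine | 1.0 | 0.75 | 0.818 | 0.841 | 0.349 |
| Migraine | 1.5 | 0.83 | 0.819 | 0.877 | 0.314 |
| Post-MO(H) | 0 | 0.50 | 0.798 | 0.800 | 0.500 |
| Post-MO(H) | 0.5 | 0.63 | 0.803 | 0.828 | 0.482 |
| Post-MO(H) | 1.0 | 0.74 | 0.804 | 0.862 | 0.438 |
| Post-MO(H) | 1.5 | 0.81 | 0.789 | 0.913 | 0.383 |

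A useless covariate costs nothing measurable. A weak one adds about 1 point (migraine) to 3 points (post-MO(H)), and a moderate one about 2 and 6.

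**5. Chance imbalance.** In 5% of trials the arms differ at baseline by more than 1.96·√(2/n) SD, in one direction or the other.

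- Post-MO(H): 1.96·√(2/152) = 0.22 SD. At an assumed log OR of 1.0 per SD, the treatment log odds ratio shifts by roughly 0.2, against a planned ln 0.50 = −0.69.
- Migraine: 1.96·√(2/283) = 0.16 SD, a shift of roughly 0.16 against ln 0.375 = −0.98.

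**6. Effect measure.** The planned rates imply marginal odds ratios of (0.04/0.96)/(0.10/0.90) = 0.375 and (0.25/0.75)/(0.40/0.60) = 0.500. The last column of the table shows that the adjusted odds ratio targets a different quantity.

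**The case against.** The strongest reply is that nothing here is wrong. Adjusting for the randomisation factors is accepted practice, the sample size assumes no covariate gain, and the type I error of the test already allows for chance imbalance. This stands. A reader might infer that the trial is underpowered or its test biased; the exact reproduction of 283 and 152, together with randomisation, rules that out.

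Second, predictive strength is assumed. Excluding current overuse (at the physician's discretion) narrows the baseline range, and a total day count mixes drug classes with thresholds of 10 and 15 days. Both could weaken the predictor. This also stands, and is why the result is given as a range.

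Third, the simulation has one covariate and no site effect, age or sex. With about 40 migraine events over about 30 sites, arm, age, sex and two new terms leave 40/5 = 8 events per fixed effect. This is a fair limit on adding both variables in that category; with intake days alone it is 40/4 = 10.

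Fourth, the opening of {20a}, with indication as a covariate, reads as one model over both categories, whereas the simulated comparison is per category. That is correct, but neither described analysis contains the baseline counts.

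Finally, a reader might say that the plan uses these variables only for subgroups, or extend the point to the monthly secondary outcomes. The text supports neither. The additional odds ratio model and the Cox model have unnamed covariates that could include the baseline counts. The secondary analyses are exploratory, and their covariates may properly be left to the SAP. The unnamed covariates do not, however, bring baseline adjustment into the confirmatory analysis.

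**Conclusion.** The point holds as a matter of efficiency. Whichever of the two descriptions in {20a} is confirmatory, it omits the baseline counts, although they are available for every randomised patient and lie on the endpoint's own scale. Under assumed log odds ratios of 0.5 to 1.5 per SD, power rises from about 0.82 to 0.83-0.88 (migraine) and from about 0.80 to 0.83-0.91 (post-MO(H)). The gain is probably small in the migraine category and may be material in the post-MO(H) category if prediction is at least moderate. These figures rest on an assumed predictor strength, a single normally distributed covariate and a model without site, age or sex. The change is worth making because it is cheap and the downside is small.

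**What to change.** Before database lock, and without sight of outcome by arm:

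1. State that the confirmatory analysis in each patient category is the logistic mixed model, so that the two descriptions in {20a} agree. Indication then drops out, being constant within a category.
2. Prespecify baseline acute-medication days as a continuous fixed effect: intake days divided by days recorded in the screening period, times 28.
3. Add baseline headache days in the same way where the event count allows. About 99 events are expected in the post-MO(H) category but only about 40 in the migraine category, so fix the rule in advance.
4. State whether the target is the conditional or the marginal odds ratio.

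The cost is wording in the protocol and SAP, one or two extra model terms, and an adjusted odds ratio that no longer estimates the marginal one unless it is standardised. No new data, visits or patients are needed.

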### *Sample size {14}*

The sample size calculation is based on the comparison of two independent proportions using a *z*-test at a significance level *α* = 0.05. Calculations were performed using PASS 13. Based on data from the literature [10–12], we estimate the transition rate from frequent EM/CM to MOH to be 10% per year, and the relapse rate after MO(H) treatment to be 40%. Plausible target occurrence rates for the treatment groups are 4% in the migraine category and 25% in the post-MO(H) category [10–12], which correspond to effect sizes (relative reduction rates) of 60% in the migraine category and 38% in the post-MO(H) category.

Aiming at a power of 1−*β*= 0.8, a sample size of N_mig_ = 2 × 283 = 566 patients for the migraine category is necessary for the ITT analysis to detect a difference in MOH occurrence proportion of 6 percentage points between patients receiving direct feedback and patients receiving unspecific messages. With the same values for significance and power as above, a sample size of N_MO(__H)_ = 2 × 152 = 304 patients for the post-MO(H) category is necessary to detect a proportion difference of 15 percentage points in MO(H) relapse.

We increased the sample size to N_mig_ = 624 and N_MO(H)_ = 336 in the studied categories to compensate for loss to follow-up; thus, a total *n* = 624 + 336 = 960 patients are to be recruited for the trial.

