#### Primary outcome

The null and alternative hypotheses are as follows for migraine patients/post-MO(H) patients:

H0 (mig): Direct specific feedback and unspecific messages compared to unspecific messages alone do not change the rate of migraine patients developing MO or MOH/relapsing after treatment of MO(H).H1 (mig): Direct feedback and unspecific messages compared to unspecific messages alone change the rate of migraine patients developing MO or MOH/relapsing after treatment of MO(H).

The primary outcome (proportion of patients with MO/MOH until end of follow-up) will be compared separately in each patient category (EM/CM patients and post-MO(H)-patients) between the treatment groups, using Pearson’s chi-square test or Fisher’s exact test, if expected frequencies are below five, aiming at demonstrating a difference to compare the null and alternative hypotheses. The null hypothesis in each group can be rejected if the two-sided *p*-value related to the appropriate test statistic is smaller than or equal to *α*=0.05. Since the hypotheses will be tested independently in each patient group, no correction factor for multiplicity needs to be applied to the significance level. In addition, the odds ratio effect of the treatment on MO(H) will be calculated in each patient category using conditional logistic regression models on the data, conditioning on matched recruitment strata, and taking into account further prognostic factors.

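### The model labelled confirmatory estimates one treatment effect across both patient categories, while the hypotheses, alpha and sample size belong to separate per-category tests; how the two relate is not stated

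*Protocol article*

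**What the plan says.** All references are to the protocol article.

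- **Statistical methods {20a}, opening paragraph.** The confirmatory analysis on the ITT set is a generalized linear mixed model with "site as random effect and age, sex, indication, and treatment arm as fixed effects". No interaction between arm and indication is listed.
- **Statistical methods, Primary outcome.** A null and an alternative hypothesis are given for migraine patients and for post-MO(H) patients. The proportions "will be compared separately in each patient category" by Pearson's chi-square test, or by Fisher's exact test when expected counts are small. "The null hypothesis in each group can be rejected if the two-sided *p*-value" is at most 0.05. No multiplicity correction is applied, on the ground that each group is tested on its own. A conditional logistic regression per category is then added to estimate the odds ratio.
- **Sample size {14}.** Each category is sized "using a *z*-test at a significance level *α* = 0.05" and "Aiming at a power of 1−*β*= 0.8".
- **Sequence generation {16a}.** Randomisation is "with stratification by indication, site, age" and sex, the same factors that appear in the mixed model.

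**The concern.** Indication can be a model term only if both categories are in the same model; within one category it is constant. With arm entered as a main effect and no interaction listed, the model has a single treatment coefficient, a weighted average over migraine and post-MO(H) patients. The hypotheses, however, are stated per category. So one analysis carries the label confirmatory, and the other carries the hypotheses, the rejection rule and the power. The article does not say whether the mixed model replaces the tests, supports them or comes before them.

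At stake is which result counts as the trial's primary finding when the two disagree. The categories have different control rates (10% and 40%) and different target reductions (60% and 38%), so unequal effects are plausible, and that is where the analyses part most often.

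**Working it through.** **1. Which analysis the sample size belongs to.** Inputs from Sample size {14}: "transition rate from frequent EM/CM to MOH to be 10% per year", with a target of 4%; "the relapse rate after MO(H) treatment to be 40" per cent, with a target of 25%; alpha 0.05, power 0.80. The test is two-sided according to the Primary outcome subsection. Pooled-variance two-proportion formula:

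n per arm = [1.960·√(2p̄(1−p̄)) + 0.8416·√(p₁(1−p₁)+p₂(1−p₂))]² / (p₁−p₂)²

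- Migraine, p̄ = 0.07: (0.7072 + 0.3016)² / 0.06² = 282.7, so 283.
- Post-MO(H), p̄ = 0.325: (1.2982 + 0.5503)² / 0.15² = 151.9, so 152.

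Both match the protocol. The stated sizes are those of the separate tests, not of the mixed model.

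**2. Whether the decisions can differ: worked counts.** For the model with indication and arm, the score test of the common treatment effect with equal arms is Z = ΣUₖ / √ΣVₖ. Here Uₖ = (control events) − tₖ/2 and Vₖ = tₖ(Nₖ−tₖ)/(4Nₖ), where tₖ is the number of events and Nₖ the number of patients in category k. At N = 566 and 304 (events, control vs intervention):

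| Migraine | Post-MO(H) | Chi-square p, migraine | Chi-square p, post-MO(H) | Pooled Z | Pooled p |
|---|---|---|---|---|---|
| 28 vs 17 | 61 vs 48 | 0.087 | 0.120 | (5.5+6.5)/√(10.36+17.48) = 2.27 | 0.023 |
| 28 vs 11 | 61 vs 61 | 0.005 | 1.00 | 8.5/√(9.08+18.26) = 1.63 | 0.10 |
| 28 vs 28 | 61 vs 38 | 1.00 | 0.005 | 11.5/√(12.62+16.69) = 2.12 | 0.034 |

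Logistic regression fits with indication and arm give the same pooled p-values to the digits shown. The rows show, in order: pooled success where neither category test succeeds; category success that the pooled test misses; and a pooled success that would be read as covering migraine patients, who show no difference at all.

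**3. How often.** Simulation of at least 200,000 trials per scenario at the recruited 312 and 168 per arm (624/2 and 336/2), each test two-sided at 0.05. The pooled test is the score test above; the Mantel-Haenszel version gives the same percentages. Assumed, because the article gives no figures: no between-site variation, no age or sex effect, no missing outcomes.

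| True effect | Pooled significant | A category test significant, pooled not | Pooled significant, neither category | Other disagreement |
|---|---|---|---|---|
| Migraine only (10% vs 4%) | 40% | 48% | 1.0% | – |
| Post-MO(H) only (40% vs 25%) | 60% | 26% | 1.4% | pooled significant, migraine not: 57% |
| Planned effects in both | 99% | 0.5% | 1.4% | pooled significant, at least one category not: 27% |

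At the pre-inflation sizes (283 and 152) the picture is the same: 47% in the first scenario, 53% for pooled significant with migraine not in the second, and 32% for partial disagreement in the third.

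**The case against.** The best defence is that only one analysis is a complete decision procedure. The Primary outcome subsection gives hypotheses, tests, alpha and a rejection rule, and the sample size fits it exactly. The mixed-model sentence has none of these. This stands, and it points to the repair. It does not remove the contradiction, because the sentence without a decision rule is the one called confirmatory. The protocol defers imputation detail, population definitions and robustness analyses to the SAP, but not the choice of deciding test. Any SAP that picks one analysis departs from one of the two passages.

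A second defence is that a common effect is inferred from a term list in a condensed article, and the SAP may add an interaction. That is fair: the claim here concerns the model as listed.

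A third is that much of the disagreement comes from scenarios with exactly no effect in one category. That is also fair. In the post-MO(H)-only scenario the non-significant migraine test is the correct answer, and in about 56 of the 57 percentage points the post-MO(H) test is significant too. The risk there is over-generalising to migraine patients, not a pooled success where both tests fail.

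Four stronger readings are tempting and are not supported:

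- *That nothing governs and success could be claimed from whichever analysis works.* The Primary outcome subsection does contain a rejection rule.
- *That the double specification seriously inflates false positives.* Two independent tests at 0.05 alone give 1 − 0.95² = 9.75%, a separate matter that the protocol addresses openly. Adding the pooled test contributes under 2 percentage points.
- *That the chi-square test wastes the precision offered by the stratification factors.* No loss can be quantified from the article, an unadjusted test after stratified randomisation remains valid, and a conditional logistic regression per category is already planned.
- *That a mixed model per category must replace the chi-square test.* At the planned rates the migraine category has about 312 × 0.10 + 312 × 0.04 ≈ 44 events over about 30 sites, so a random-site model there is debatable.

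**Conclusion.** The contradiction is real and lies in text the protocol has already fixed: the analysis labelled confirmatory cannot, as listed, decide either category hypothesis, and the analysis that can is not labelled so. The two can reach different decisions, meaning significant versus not significant. A reader might take this to mean significant effects in opposite directions, which neither the documents nor the calculations show.

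The size depends on how far the effects differ between categories. It is large when only one category benefits (about 48% and 57%) and moderate under the planned effects (about 27% partial disagreement), where complete conflict is rare (1.4% pooled only, 0.5% category only). These percentages rest on the assumptions of no site, age or sex effects and complete outcome data. The contradiction itself rests on none of them.

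**What to change.** In both parts of the statistical methods section and in the SAP, before unblinding:

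1. State that the within-category test decides each category's hypothesis. This can be the Pearson or Fisher test already described, which matches the sample size, or a prespecified covariate-adjusted version of it.
2. Remove the word confirmatory from the pooled mixed model.
3. Keep that model as supportive, with an arm-by-indication interaction and a treatment contrast reported for each category.

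The cost is rewording and alignment with the SAP. No extra patients or data are needed, and the sample size stays as it is if the chi-square test is kept as the deciding test.
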